## Methods/design

The present project is designed as a selected and indicated prevention program: children and adolescents at high risk for developing affective disorders will be identified and treated if they run an ultra high risk. Such an approach results in a relatively powerful design [24]. The study is further designed as a randomised controlled trial (RCT), including an intervention condition and a minimal information condition.

### Participants

Participants in the study are children of patients with and anxiety or mood disorder. We aim at screening 554 children (T0), and at including 204 children in the intervention phase of the study. We have designed in- and exclusion criteria for parents and children:

Inclusion criteria (parents):

At least one of the biological parents, currently or in the past five years, treated for a unipolar mood disorder or an anxiety disorder; informed consent.

Exclusion criteria (both parents):

Mental retardation; severe alcohol or substance use disorder; schizophrenia or other primary psychotic disorder; schizoaffective disorder; bipolar disorder.

Inclusion criteria for the intervention phase (offspring): age 8–17; being at ultra high risk for developing a mood or anxiety disorder. Two pathways lead to the qualification of “ultra high risk”: (1) children report elevated symptoms of anxiety or depression, as defined as the 80^th^ percentile of either the subscale Depression or the cluster of subscales of Anxiety on the RCADS self-report. We used data from the large Dutch epidemiological study TRAILS to set these cut-offs at the various age segments (Tracking Adolescents’ Individual Lives [38]). (2) Children meet at least 2 of 3 criteria of our High Risk Index that was developed in the ARIADNE sample: (a) being female, (b) having two affected parents, (c) having a parent with (past) suicidal behaviour.

Exclusion criteria (offspring): mental retardation; not speaking Dutch fluently; severe alcohol or substance use disorder; current diagnosis of a mental disorder that warrants regular treatment. Children with a history of a mental disorder are included, as well as children with a current disorder that had sufficiently been treated (e.g. in the case of stable medication for ADHD).

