**Discussion:**

The current intervention trial aims to significantly reduce the risk of intergenerational transmission of mood and anxiety disorders with a short and well targeted intervention that is directed at strengthening the resilience in potentially vulnerable children. We plan to evaluate the effectiveness and cost-effectiveness of such an intervention and to identify mechanisms of change.

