### Trial objective and purpose

The primary goal is to investigate whether a brief (10 + 2 sessions) cognitive behavioural treatment program on resilience and symptom reduction can prevent the incidence of depression or anxiety disorder in an ultra high risk sample of 8–18 year old offspring of patients with unipolar depression or anxiety disorder (sample defined by a High Risk Index or subclinical symptoms, or both). The second goal is to examine whether this intervention meets current standards for cost-effectiveness. A third goal is to explore the role of a number of factors that may potentially mediate or moderate the effect of the intervention. Mediating factors include coping, attributional style, daily activities, and optimism, while the selected moderating variables are child temperament characteristics and executive functioning, parental psychopathology (of both parents), child symptomatology, attachment, and (automatic) self-associations.

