#### Measures

##### Primary outcome

Our primary outcome is the time to onset of depression or anxiety disorders in the offspring, based on the Child version of **Diagnostic Interview Schedule for Children** Version IV NIMH DISC-IV; [40], which is a highly structured diagnostic assessment instrument designed to gather symptom presence for child and adolescent psychiatric disorders based on the symptoms and criteria variables as defined in the Diagnostic and Statistical Manual of Mental Disorders DSM-IV; [41]. The computerized DISC is administered via a computer (the interviewer reads questions from the computer screen and enters responses directly into the computer) and scored by computer algorithm [42]. There are parallel versions of the instrument: the DISC-P for parents, and the DISC-C for direct administration to children. In the present study the DISC-C is used to assess anxiety disorders and depression, and a brief assessment of alcohol and drug use. The DISC-P is used as a parent report of children’s anxiety and depression symptoms as well as questions about whole life symptomatology. At the 12- and 24-follow-up assessments, the interviewer addresses the past 12 months. If any disorder was present, the interviewer makes an estimation of the time of onset and the duration of the disorder. The interviewer combines information retrieved from the DISC with the **Weekly Emotions Diary for Youth (WEDY;** [name] & [name], Weekly Emotions Diary, unpublished manuscript**)** as input. All children included in the intervention trial are asked to keep a weekly diary during the study, giving scores of three items: anxiety, sad mood, and happiness on a 0–5 scale. This chart was developed for the purpose of the current study, primarily as a helpful tool to obtain a good estimate of the onset and duration of a disorder (if present by DISC-criteria), since children may not always have an adequate sense of time when retrospectively reporting over the past year. Children are encouraged to fill out the diaries either on paper or through the internet in a web-based diary. They receive an incentive of 1 euro per month for completing the weekly diary, with a maximum of 25 euros.

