### Sample size calculation

Our sample size calculation is based on the conventional significance (alpha) and power (1-beta) levels of 0.05 and 0.80 respectively, planning one-sided testing. We assume a baseline incidence rate of mood and anxiety disorders of 0.11/person*year for the control condition, based on our own unpublished analyses in high risk offspring from the ARIADNE study; in the ultra-high risk subgroup of children with 2 or 3 risk factors we found a 10-year cumulative incidence of anxiety- and mood-disorders of 0.67 (time frame: age 10–20), which corresponds to an incidence rate of 0.11/person*year, assuming a constant rate. With an intended follow-up duration of 2 years, we would then need a minimum of 81 participants per condition to give our study sufficient power to detect a clinically meaningful effect of the intervention on the time to onset of episodes of mood- and anxiety disorders. We compared our estimated incidence rates with two prevention studies. Clarke et al. [13], who studied the effect of a preventive program in subsyndromal offspring of depressed patients, found a 1 year cumulative incidence of 0.25 for depression alone (rate 0.29/person*year). Therefore, our incidence assumption is relatively conservative. We assume a risk reduction of 70% for the treatment condition, based on the Clarke study; the 1 year cumulative incidence of depression in the intervention group is 0.08, compared to 0.25 in the control group (unadjusted hazard ratio 0.29). The reported adjusted hazard ratio in this study is 0.18. Dadds et al. [67] report a hazard ratio of 0.22 in favor of a program aimed at preventing anxiety disorders in children. Again, we choose the more conservative estimate. Nevertheless, realizing that above-mentioned assumptions remain uncertain and that participants may drop out, we decided to include another 25%, resulting in 2 groups of 102 children for the intervention phase (N = 204).

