### Statistical analyses

Survival analysis will be used to answer the first research question (effect of treatment on the possible onset of depression or anxiety disorder). It encompasses a wide variety of methods for analyzing the timing of events. The logrank test (sometimes called the Mantel-Cox test) is a hypothesis test and will be used to compare the ‘survival’ distribution between the intervention and the control group. The measurement is the time to event (clinical onset of anxiety disorder or depression). Therefore ‘survival’ is ‘no onset of an anxiety or mood disorder’ in the study period of 2 years.

All data will be analyzed using the intent-to-treat principle. Multilevel analysis is a general term referring to statistical methods appropriate for the analysis of data sets comprising several types of units of analysis. Multilevel analysis holds two important features that are relevant to our data, namely the handling of missing data, as well as the possibility to work with dependent data. In our case, siblings are dependent (“nested”) data and can be analyzed as such. Intention to treat analyses are done to avoid the effects of crossover and drop-out, which may break the randomization to the treatment groups in the study. Mediators and moderators can be included as explanatory variables into the multilevel model.

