## Discussion

Given the high prevalence of anxiety and mood disorders in offspring of adults with these disorders, prevention interventions are needed to prevent internalising mental disorders in children and adolescents. The current STERK-study is a randomised controlled prevention trial in high-risk offspring (aged 8–17 years) of anxious and depressed patients. We select youth on either elevated symptoms or on the basis of the High Risk Index that we developed in an earlier epidemiological offspring study (ARIADNE). The present study is the first to focus on both anxiety and depression, since these disorders are often comorbid, and since epidemiological findings in offspring show that anxious and depressive symptoms are prevalent in offspring of patients with anxiety disorders [30] and just as well in patients suffering from unipolar depression [31]. With this study, we hope to contribute to the prevention of mental disorders in offspring, as well as to the knowledge on mediators and moderators of change.

Developing prevention studies, getting funding, gaining ethical approval, and including participants is a time-consuming trajectory. For the current study/project, the grant application was in 2007, the grant was awarded in 2008, and we received ethical approval by the end of 2009. The inclusion of participants into the project is still ongoing. Due to this timeframe, we have not been able to incorporate some of the most recent findings into our design. In fact, the current design is an adaptation of an earlier design. In the first wave of the study, we only included adult patients that were currently in treatment, and we excluded all children with a history of mental illness. However, we noticed that quite some eligible and interested participants were excluded in this way. In addition, the Garber study [14] got published in 2009, showing that prevention interventions may be only fruitful if parents were remitted in terms of their own mental health problems. Therefore, we decided to broaden the inclusion scope of our trial (approved of by both the governmental funding organization ZonMw and the Medical Ethical Committee).

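### The aim is worded as preventing incidence and transmission, but children with a past mood or anxiety disorder can enrol, so the pooled primary test alone cannot show prevention of first onset

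*Protocol article*

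**What the plan says.** - **Aim.** Under Trial objective and purpose, the question is whether the programme "can prevent the incidence of depression or anxiety disorder in an ultra high risk sample". The Discussion paragraph of the Abstract says that the trial "aims to significantly reduce the risk of intergenerational transmission of mood and anxiety disorders".
- **Event.** Under Primary outcome: "Our primary outcome is the time to onset of depression or anxiety disorders in the offspring". Under Statistical analyses: "Therefore ‘survival’ is ‘no onset of an anxiety or mood disorder’ in the study period of 2 years". Neither section separates a first episode from a later one. The Sample size calculation uses a different phrase, "the time to onset of episodes of mood- and anxiety disorders".
- **Who is enrolled.** Under Participants: "Children with a history of a mental disorder are included, as well as children with a current disorder that had sufficiently been treated". The main Discussion explains that this is a change. In the first wave, "we only included adult patients that were currently in treatment, and we excluded all children with a history of mental illness"; the criteria were then broadened with the approval of the funder and the ethics committee.
- **Handling of history.** The Randomisation section stratifies by centre and by pathway of inclusion. Lifetime disorder is not among the moderators listed in the objectives. The Primary outcome section says that the parent interview (DISC-P) also asks about lifetime symptoms.

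**The concern.** In a child who has already had a depressive or anxiety disorder, a new episode is a recurrence, and whatever transmission there is from the parent has already taken place. Counting that episode is a legitimate choice, but it answers a different question from incidence. In the first wave no child had a history, so events were first onsets. After the widening they can be either. The wording of the aim was not brought into line with the new population.

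At stake is the conclusion. A pooled result mixes primary prevention with prevention of recurrence, and the stated aim invites the reader to take it as the former. The 10-year Markov model in the Economic evaluation is also affected. It draws on trial data and allows for relapse and remission, and a pooled effect does not tell it whether first onset, recurrence or both were changed.

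**Working it through.** **1. The plan's own sample size.** Inputs from the Sample size calculation: 10-year cumulative incidence 0.67, 2 years of follow-up, 70% reduction (hazard ratio 0.30), one-sided alpha 0.05, power 0.80.

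- Rate: −ln(1 − 0.67)/10 = 0.111 per person-year, as stated (0.11).
- Two-year event probabilities: control 1 − exp(−0.22) = 0.1975; intervention 1 − exp(−0.066) = 0.0639; sum 0.2614.
- Freedman events: (1.645 + 0.842)² × (1.30/0.70)² = 6.18 × 3.449 = 21.3.
- Per arm: 21.3/0.2614 = 81.6. The exponential-rate (Lachin) formula gives 80.6, that is, 81.
- Inflation: 81 × 1.25 = 101.25, that is, 102.

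The stated 81 and 102 therefore reproduce. The point exposes no arithmetic error.

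**2. How many events could be recurrences.** The document gives neither the share p of children with a past mood or anxiety disorder nor the ratio r of their event rate to that of never-affected children. Both are assumptions. On the rates, with the same treatment effect in both groups, the recurrent share is p·r/(p·r + 1 − p). The last column instead counts at most one event per child over 2 years, in both arms, at the planned rates (never-affected children 0.11 and 0.033; children with a history r times these).

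| p | r | From the rates | Over 2 years, both arms |
|---|---|---|---|
| 0.10 | 2 | 0.2/1.1 = 18% | 17% |
| 0.20 | 2 | 0.4/1.2 = 33% | 31% |
| 0.30 | 2 | 0.6/1.3 = 46% | 44% |
| 0.30 | 3 | 0.9/1.6 = 56% | 52% |

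**3. What a first-onset analysis could detect.** Restrict to children with no past mood or anxiety disorder, keep the planned rates and hazard ratio 0.30, and use power = Φ(√d × 0.70/1.30 − 1.645), with d = n × (1 − p) × 0.2614 and n children per arm.

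| p | d at n = 102 | Power, n = 102 (no dropout) | Power, n = 81 |
|---|---|---|---|
| 0.10 | 24.0 | 0.84 | 0.76 |
| 0.20 | 21.3 | 0.80 | 0.72 |
| 0.30 | 18.7 | 0.75 | 0.67 |

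With no history at all and n = 102, d is 26.7 and power is 0.87.

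**The case against.** A reader might infer that the trial cannot show prevention of onset at all. The document does not support that. It nowhere defines onset as first lifetime onset, and the Sample size calculation speaks of episodes. The Background describes two offspring trials that admitted youngsters with past depression, and it lists their results under onset of disorder. One of them is the source of the 70% effect. The authors' own usage thus already covers recurrence, and the randomised comparison is sound for that endpoint.

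Three further limits stand. The Participants section admits a history of any mental disorder, with stable ADHD medication as the example for a treated current disorder; only a past mood or anxiety disorder can yield a recurrence. A higher event rate in such children would add events, not remove power. And leaving history out of the randomisation strata does not bias the test.

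A reader might also infer that a positive result would come mainly from recurrences. One can construct this: with 30% history, rate ratio 2, and hazard ratios of 0.3 for recurrence and 0.8 for first onset, the event-weighted hazard ratio is about 0.46 × 0.3 + 0.54 × 0.8 = 0.57. But all four inputs are invented, and nothing in the document suggests such a split.

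Finally, covariates and sensitivity analyses are often left to an analysis plan that is not shown. That is fair for the detail. It does not remove the mismatch between aim, eligibility and event, which lies within this one document.

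**Conclusion.** The point holds in a limited form. The aim speaks of incidence and transmission, eligibility admits children with a past mood or anxiety disorder, and the primary event does not tell first onset from recurrence. The pooled log-rank test supports a conclusion on new episodes of either kind; a conclusion on first onset or transmission needs more than that test.

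The size cannot be read from the document. Under the assumptions shown (10% to 30% history, rate ratio 2 to 3), roughly one sixth to just over one half of events would be recurrences. The true share would be lower to the extent that first-wave children, who had no history, make up the sample, and to the extent that the histories admitted are of other disorders. The planned sample size and the validity of the randomised comparison are not in question.

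**What to change.** 1. In Trial objective and purpose, Primary outcome and Statistical analyses, define the primary event as a new episode of mood or anxiety disorder, whether first onset or recurrence.
2. Stratify or adjust the primary comparison for lifetime mood or anxiety disorder at T1. The DISC-P already asks about lifetime symptoms; state how a lifetime diagnosis is derived from it. With only some 21 to 27 events expected at the planned rates (81 × 0.2614 to 102 × 0.2614), a single yes/no term is enough. The randomisation strata can stay as they are.
3. Pre-specify a secondary analysis of time to first onset in children with no lifetime mood or anxiety disorder at T1.
4. Rest statements on incidence or intergenerational transmission on that secondary analysis, and say so in advance.

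The cost is some wording and one extra analysis on data already collected. The downside is that the first-onset analysis has fewer children and a wider interval. At 102 per arm it keeps power of 0.80 only if about 20% or fewer have such a history and nobody drops out, which is why it suits a secondary role.

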### Procedure

The study has two phases, namely the screening phase and the intervention phase. Details on the procedure are described in the flow diagram (Figure 1).

**Figure 1 F1:**
[figure not shown]
Flow diagram.

#### Referral and recruitment

Adult patients are recruited through mental health services, general practitioners, and by media (newsletters, social media, website, media attention through interviews for newspapers and radio). Adult and child mental health services participate in the recruitment of participants. In child mental health services, parents are included if they have an anxiety or mood disorder themselves. All children of these parents can participate in the study.

#### Informed consent

Adult patients are informed about the study in two ways. First, patients within a mental health care centre (adult or youth) are informed about the study by their therapist by a full information letter, containing all information for both the parents and the children. If the patient is interested in participating, he or she can contact the researcher. The researcher then checks whether the family has understood the information on the trial. If so, the consent form is signed by both parents and children, and the family is invited for the first screening. Separate informed consent forms are available for parents, adolescents (secondary school) and children (primary school). Even though informed consent is not warranted under the age of 12 in the Netherlands, we do have younger children sign informed consents so that we are sure they are fully informed about the study.

Second, patients may contact the researchers directly, after having received information about the study via their general practitioner, the media, or the website. In that case, the researcher directly informs the family members about the study by way of the information letters described above. We then check the status parent’s past and current psychopathology through a brief telephone interview. Note that for all parents the exact diagnosis is obtained during the assessments through a structured diagnostic interview (CIDI).

Participants can always draw back from participating in the study, at any time during the assessment or intervention, without giving a reason for their withdrawal. Withdrawal from the trial will not affect the regular mental health care for either themselves or their children.

#### Randomisation

Since outcome may be dependent on treatment centre and the pathway of inclusion (through elevated symptoms versus no symptoms/HRI only), we decided to work with stratified allocation to treatment condition to ensure a balanced number of participants over conditions. A web-based computer program allows for dynamic on-the-spot randomisation. Randomisation is based on the defined strata as well as on the assigned treatment condition of earlier subjects within the strata. To prevent conscious or unconscious influence on the recruiting team, we choose to conceal the exact details of the randomisation process at this stage (following the recommendations of the CONSORT guidelines [39]). Randomisation takes place after the whole assessment has been completed, so that the first assessment is not dependent on the participant’s knowledge of treatment condition. The research assistant assigns a unique code to each participant. In case one family has several high risk children, the youngest child is entered for randomisation, and the siblings are assigned to the same condition. The research assistant then enters the number of the participant in the web-based randomisation program, and at that moment the computer randomly assigns the treatment condition (active intervention or minimal information; 1:1).

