The third study investigated the effectiveness of a family program, including the 8–15 year-old offspring of at least one parent with an episode of depression in the past 18 months [16]. At least one of the children in the family needed to be free of a depressive disorder. The 6–11 session family program was compared to two plenary group lectures for parents. Both interventions advocated open discussion about the parental illness and were directed at change in family dynamics. Both interventions proved equally effective in increasing family functioning and decreasing internalising behaviours up to 4.5 year follow-up (based on 105 families) [18]. Families in the more intensive treatment reported more benefits in parent-child behaviours and regarding the child’s understanding of parental mental illness.

The fourth trial also investigated the effectiveness of a family intervention for families with at least one parent with a history of depression [19]. The children did not need to report symptoms themselves to participate in the study. Participants included 111 families with 155 children aged 9–15 years, who were randomized to either written information only or to a 12-session cognitive behavioral family intervention in a group format [19]. The family intervention focused on enhancing awareness of the role of depression in a family, on ameliorating parent–child interactions by teaching parenting skills (focusing on parental warmth and structure), and on learning general coping skills (for parents and children separately). Results indicate that children in the family program showed more benefits in terms of internalizing and externalizing symptoms in both parent and child reports. These gains were maintained at two year follow-up [20].

The only trial so far focusing on offspring of patients with anxiety disorders included 40 children aged 7–12 years, who were randomized to either an 8-session family-based CBT program focusing on coping and strengths or to a waitlist control condition. Children were not allowed to have a current anxiety disorder. Current or past symptomatology was not warranted for inclusion in the study. This trial was successful in preventing the onset of anxiety disorders in the offspring: offspring in the active condition did not develop anxiety disorders, whereas 30% of waitlist children met criteria for an anxiety disorder at 1 year follow-up.

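### Siblings are allocated together and acknowledged as dependent, but the named primary log-rank test and the 81-per-arm calculation treat children as independent

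*Protocol article*

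**What the plan says.** Four parts of the protocol article bear on this.

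- **Referral and recruitment** lets all children of a recruited parent take part.
- **Randomisation** sets the rule for families with several high-risk children: "the youngest child is entered for randomisation, and the siblings are assigned to the same condition". Such a family is one unit of allocation.
- **Statistical analyses** names the test for the first research question: "The logrank test (sometimes called the Mantel-Cox test) is a hypothesis test and will be used to compare the" time-to-onset distributions of the two arms. No family term, stratum or robust variance is attached to it. The next paragraph introduces multilevel analysis and notes that siblings are nested and may be analysed accordingly. It does not link that method to the log-rank test or to time to onset.
- **Sample size calculation** works from "significance (alpha) and power (1-beta) levels of 0.05 and 0.80 respectively, planning one-sided testing", a control rate, an effect and two years of follow-up, and concludes that "we would then need a minimum of 81 participants per condition". A further 25% is added because the assumptions are uncertain and participants may drop out, giving 102 per arm. Siblings are not mentioned.

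**The concern.** The standard log-rank variance assumes that children contribute independent information. Siblings in this trial share an arm, and full siblings share two of the three High Risk Index criteria (two affected parents, parental suicidal behaviour). They also share a household. Some positive correlation in onset is therefore plausible. When positively correlated children are always placed in the same arm, the true variance of the log-rank statistic exceeds the one used, and the test rejects too often under the null.

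This is the test of the primary outcome. It is one-sided at 0.05 and planned on only about 21 events, so an understated variance bears directly on the main conclusion. A test that does allow for family has less power than the calculation states for the same number of children.

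**Working it through.** **1. Reproducing the plan's 81 per arm**

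Inputs from the Sample size calculation section:
- One-sided alpha 0.05 and power 0.80.
- Control rate: "We assume a baseline incidence rate of mood and anxiety disorders of 0.11/person*year for the control condition". This agrees with its source, since −ln(1 − 0.67)/10 = 0.1109 per year.
- Effect: "We assume a risk reduction of 70% for the treatment condition", read as a hazard ratio of 0.30.
- Follow-up of 2 years for every child.

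Freedman formula for the log-rank test:
- Events = [(1.645 + 0.842) × (1 + 0.30)/(1 − 0.30)]² = 21.3.
- Two-year risk, control = 1 − exp(−0.22) = 0.1975; intervention = 1 − exp(−0.066) = 0.0639; sum 0.2614.
- n per arm = 21.3/0.2614 = 81.6, or 81.0 with the unrounded rate of 0.1109.
- 81 × 1.25 = 101.25, rounded up to 102.

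The plan's figure is thus reproduced for independent children, with no sibling allowance in it. At exactly 81 per arm the formula gives power 0.797.

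**2. Allowing for siblings**

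The article gives neither the mean number of randomised children per family (m) nor the ICC. Both are assumptions here.

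- Design effect: DE = 1 + (m − 1) × ICC.
- n per arm needed: 81 × DE, rounded up.
- Actual one-sided error of the unadjusted test: 1 − Φ(1.645/√DE).
- Power of a clustered test with n per arm: Φ(√(n × 0.2614/DE) × 0.70/1.30 − 1.645).

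| m | ICC | DE | n per arm needed | Actual one-sided error | Power at 81 per arm | Power at 102 per arm, full follow-up |
|---|---|---|---|---|---|---|
| 1.2 | 0.1 | 1.02 | 83 | 5.2% | 0.79 | 0.87 |
| 1.4 | 0.2 | 1.08 | 88 | 5.7% | 0.77 | 0.85 |
| 1.6 | 0.3 | 1.18 | 96 | 6.5% | 0.74 | 0.82 |
| 2.0 | 0.5 (extreme) | 1.50 | 122 | 9.0% | 0.65 | 0.73 |

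At 102 per arm with nobody lost, power falls to 0.80 at DE = 1.25.

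**3. Unequal family sizes**

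When family sizes vary, the size-weighted mean belongs in the formula, and it is larger than the simple mean. As an illustration, one family trial described in the Background section had "111 families with 155 children", or 1.4 per family. A 60/40 split of one- and two-child families gives (0.6 × 1 + 0.4 × 4)/1.4 = 1.57. A 70/20/10 split of one, two and three children gives (0.7 + 0.8 + 0.9)/1.4 = 1.71. At ICC 0.2, DE becomes 1.11 to 1.14 and the error 6.0% to 6.2%, against 5.7% in the table. At ICC 0.3 and 1.71, DE is 1.21 and the error about 6.8%.

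**4. Simulation check**

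The unadjusted log-rank test was simulated at 81 per arm, 6,000 trials per setting, with correlated sibling pairs. Its one-sided error was about 0.05 without siblings. With 70% of children in pairs it was 0.058 and 0.071 at latent correlations of 0.3 and 0.6. With all children in pairs it was 0.068 and 0.084. Power of the unadjusted test fell only from about 0.82 to 0.80. The harm to the test as named is therefore mainly false-positive inflation; the loss of power belongs to a test that corrects for it.

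**The case against.** **The plan already recognises the dependence, and a fuller analysis plan may exist.** The multilevel paragraph is not restricted to secondary outcomes, and an article may leave the implementation to the analysis plan. This stands in part: the authors did not overlook siblings. But the article names a specific primary test and a specific sample size, and neither fits its own allocation rule. Applying the sibling adjustment to time to onset would change that test, not merely add detail to it.

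**The number of siblings may be small.** The recruitment arithmetic takes 20% of 2770 patient files, which is 554, and this equals the 554 children to be screened: about one child per participating patient. Each sibling must also qualify separately, and only 204 of 554 (37%) are expected to be randomised. The figure of 1.4 comes from a different trial. This stands, and it is why the size cannot be pinned down.

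**The correlation may be modest.** Selecting on shared parental risk makes families more alike, which tends to lower residual correlation, and entry also depends on the child's sex and own symptoms. With a control risk of 0.1975, an ICC of 0.5 would mean a risk of 0.1975 + 0.5 × 0.8025 = 0.60 for a child whose sibling is affected, which is extreme. This stands as a reason to treat the high-correlation rows as limits.

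**The 25% margin covers it.** It would, up to DE of about 1.25, if no child were lost. The article assigns that margin to uncertain assumptions and drop-out, so it cannot be counted in full a second time.

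**Conclusion.** The mismatch is real and of moderate weight; it is not a defect that must be repaired before the trial can stand. Children are allocated by family and acknowledged as dependent, yet the named primary test and its sample size assume independence. The direction follows from same-arm allocation and positive within-family correlation. The size depends on assumed inputs: a one-sided error of about 5.2% to 6.5% for a mean of 1.2 to 1.6 children per family and an ICC of 0.1 to 0.3, 7% or more only with high correlation or many siblings, and negligible inflation if few families contribute siblings. For a clustered test, power at 81 per arm is about 0.74 to 0.79.

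A reader might infer more, but the article does not support it:
- That the trial as enrolled is clearly underpowered. At 102 per arm with full follow-up, power stays at about 0.80 or above up to DE 1.25.
- That published confidence intervals will be too narrow. The Statistical analyses section plans a hypothesis test for the primary question and states no interval.
- That the bootstrap in the Economic evaluation section wrongly resamples children. Its resampling unit is not specified, which is ordinary analysis-plan detail.

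**What to change.** In the Statistical analyses section, make the primary time-to-onset test family-robust. Suitable choices are a log-rank score test or Cox model with variance clustered on family, or a Cox model with shared frailty by family. Choose one before outcomes are analysed, and say that the acknowledged sibling dependence is handled this way for the primary outcome.

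In the Sample size calculation section, state an assumed number of siblings per family and an ICC, give the design effect, and restate the power at 81 and 102 per arm after allowing for expected drop-out.

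The cost is a wording change and a family identifier in the dataset. Standard errors become slightly wider and the stated power slightly lower. No extra enrolment is needed.
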